### **How do I store SPIRIVA HandiHaler?**

- **Do not store SPIRIVA capsules in the HandiHaler device.**
- Store SPIRIVA capsules in the sealed blister package at room temperature [68°–77°F (20°–25°C)].
- Keep SPIRIVA capsules away from heat and cold (do not freeze).
- Store SPIRIVA capsules in a dry place. Throw away any unused SPIRIVA capsules that have been open to air.

Ask your doctor or pharmacist if you have any questions about storing your SPIRIVA capsules.

**Keep SPIRIVA HandiHaler, SPIRIVA capsules, and all medicines out of the reach of children.**

### **General information about SPIRIVA HandiHaler**

Medicines are sometimes prescribed for purposes other than those listed in Patient Information leaflets. Do not use SPIRIVA HandiHaler for a purpose for which it has not been prescribed. Do not give SPIRIVA HandiHaler to other people even if they have the same symptoms that you have. It may harm them.

For more information about SPIRIVA HandiHaler, talk with your doctor. You can ask your doctor or pharmacist for information about SPIRIVA HandiHaler that is written for health professionals.

For more information about SPIRIVA HandiHaler, you may also call [name] or (TTY) [name].

**What are the ingredients in SPIRIVA HandiHaler?**

Active ingredient: tiotropium

Inactive ingredient: lactose monohydrate

**What is COPD (Chronic Obstructive Pulmonary Disease)?**

COPD is a serious lung disease that includes chronic bronchitis, emphysema, or both. Most COPD is caused by smoking. When you have COPD, your airways become narrow. So, air moves out of your lungs more slowly. This makes it hard to breathe.

Distributed by:

Boehringer Ingelheim Pharmaceuticals, Inc.  
[name]

Marketed by:

Boehringer Ingelheim Pharmaceuticals, Inc.  
[name]

and

Pfizer Inc  
[name]

Licensed from:

Boehringer Ingelheim International GmbH

SPIRIVA® and HandiHaler® are registered trademarks and are used under license from Boehringer Ingelheim International GmbH.

©Copyright 2009 Boehringer Ingelheim International GmbH  
ALL RIGHTS RESERVED

SPIRIVA® (tiotropium bromide inhalation powder) is covered by U.S. Patent Nos. RE38,912, RE39,820, 5,478,578, 6,777,423, 6,908,928, 7,070,800, and 7,309,707 with other patents pending. The HandiHaler® device is covered by U.S. Design Patent No. D355,029 with other patents pending.

IT1600TC1109

10004551/06

65626-06

Revised March 2009

**A copy of these instructions and patient information will be given to the patient.**

## 10.2 INSTRUCTINS FOR USE OF THE METERED DOSE INHALER (ALBUTEROL)

**Patients will be instructed for the use of the MDI as follows:**

- 1. SHAKE THE INHALER WELL** immediately before each use. **Then remove the cap from the mouthpiece. Check mouthpiece for foreign objects prior to use.** Make sure the canister is fully inserted into the actuator.
- 2.** As with all aerosol medications, it is recommended to prime the inhaler before using for the first time and in cases where the inhaler has not been used for more than 2 weeks. Prime by releasing four “test sprays” into the air, away from your face.
- 3. BREATHE OUT FULLY THROUGH THE MOUTH**, expelling as much air from your lungs as possible. Place the mouthpiece fully into the mouth, holding the inhaler in its upright position and closing the lips around it.
- 4. WHILE BREATHING IN DEEPLY AND SLOWLY THROUGH THE MOUTH, FULLY DEPRESS THE TOP OF THE METAL CANISTER** with your index finger.
- 5. HOLD YOUR BREATH AS LONG AS POSSIBLE**, up to 10 seconds. Before breathing out, remove the inhaler from your mouth and release your finger from the canister.
- 6.** If your physician has prescribed additional puffs, wait 1 minute, shake the inhaler again, and repeat steps 2 through 4. Replace the cap after use.
- 7. KEEPING THE PLASTIC MOUTHPIECE CLEAN IS EXTREMELY IMPORTANT TO PREVENT MEDICATION BUILDUP AND BLOCKAGE. THE MOUTHPIECE SHOULD BE WASHED, SHAKEN TO REMOVE EXCESS WATER, AND AIR DRIED THOROUGHLY AT LEAST ONCE A WEEK. INHALER MAY STOP SPRAYING IF NOT PROPERLY CLEANED.**

A copy of the patient instructions for each participating country will be filed in the ISF. A copy of these instructions will be given to the patient.

### 10.3 EXERCISE TESTS

During the initial Screening Visit (Visit 1), an incremental exercise test (IET) will be performed on a treadmill to a symptom-limited maximum (maximum work capacity). In following visits (V2, V3, V4, V5 and V6), a constant work rate exercise endurance test, (symptom-limited endurance exercise test) will be performed in a similar manner at the same constant work rate equal to 80% of the maximum work rate achieved at the IET. During all exercise tests, including the incremental test and all constant work rate tests, the extent of dynamic hyperinflation will be assessed by serial inspiratory capacity measurements (IC). Specific details of the exercise tests are described in the Exercise Testing and Quality Control Manual of Procedures filed in the ISF.

#### **General Considerations for Exercise Testing**

Exercise testing equipment will be standardized across study centers to minimize the between-laboratory variability and the technical oversight and quality control can be conducted efficiently. Standardization will eliminate the need for developing technical details for the use of different equipment. In this study all exercise testing will be conducted on treadmill using the Linear Treadmill Protocol that has been developed at the Los Angeles Biomedical Research Institute. In this trial, patients with COPD will perform 10 W/min and the age / gender matched controls will perform 15 W/min ramp test. The constant work rate will be 80% of peak work rate in both populations.

#### ***Treadmill equipment***

- It is a requirement that the treadmill used in this protocol can be electronically connected to the metabolic and cardiac monitoring equipment so that the subject-specific protocol can be programmed and the actual treadmill parameters be read by the computer of the monitoring equipment.
- The treadmill must have a speed range of up to 16 km/h in 0.2 km/h increments; the slope range is from 0-25% grade; carrying capacity of 180 kg and the walking surface is about 56 cm by 160 cm.
- Calibration of the treadmill must be performed prior to the study (within 6 months). In addition, calibration should be performed if the treadmill is moved or when unusual response profiles raise concerns about the equipment, and/or after any service is done on the treadmill. Documentation of calibration of the equipment must be on file.
- Quality control of the exercise equipment will be performed using a healthy, non-smoking member of the laboratory staff on a regular basis. (See the Exercise Testing and Quality Control Manual of Procedures filed in the ISF for details.) The physiological validation will be done on two constant work rate levels as it is detailed in the Exercise Testing and Quality Control Manual of Procedures filed in the ISF. The results of the physiological validation studies will be used for two purposes: a.) to ensure that all equipments (treadmills and CPET systems) used at all centers are accurate and b.) to establish the precision at each laboratory and across laboratories in the study. The physiological validation studies will be part of source documentation.

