## 2.4 OTHER ENDPOINTS

Other endpoints which will explore the differences between early stage COPD patients and Age / Gender Matched Controls are:

- Maximum work rate during incremental exercise test
- Percentage of patients with respiratory limitation (as defined by Breathing Reserve <15 L/min)
- Ventilatory and respiratory mechanics, metabolic parameters, breathing pattern and operating lung volumes during constant work rate exercise as described in Section 5.1.2.
- Measured diffusing capacity for carbon monoxide in early stage COPD compared to Age / Gender Matched Controls
- Dyspnea intensity during physical exercise: Modified Borg Scale (at isotime, isoventilation and at end exercise)
- Leg discomfort during physical exercise: Modified Borg Scale (at isotime, isoventilation and at end exercise)
- Locus of symptom limitation (breathing limited vs. leg limited vs. both)
- BDI dyspnea scale
- Physical activity and quality of life assessment: WPAI-GH, FACIT- short form, VSAQ and accelerometer measurements.
  - Correlation analyses of activity monitor outputs, including measures of physical activity and active energy expenditure over time with: (a) clinical endpoints, (b) respiratory symptoms scores and (c) physical activity questionnaires will be conducted.

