## INCREMENTAL EXERCISE CHALLENGE

In addition to adhering to the general considerations for exercise challenges described above, the following specific procedures should also be adhered to while preparing the test at Visit 1. The incremental ramp protocol for the COPD patients will be uniformly 10 W/min and 15 W/min for the age/ gender matched control subjects. The individualization will be programmed into the RDC system. This will assure that the laboratories will be provided with the parameters of the appropriate protocol the parameters of which will be entered in testing system.

The programmed exercise challenge test protocol provides a total of 15 steps. The target work rate (100 Watts in the COPD group and 150 Watts in the control group) is reached in the 10th step and additional 5 steps for further incrementing the work rate with the same slope. This design allows for each subject to perform the same work rate increment utilizing the same speed-range, regardless of the subject's weight, thus providing a comfortable walking speed throughout the test for everybody.

The speed will be incremented linearly from 0.6 mph to 2.2 mph in the expected range and reaches a maximum of 4 mph in the extended range. The steps of the inclination are calculated based on linearly incremented speed and work rate steps; resulting in a non-linear increase in the treadmill grade.

Entering the appropriate values in the appropriate page on the eCRF, the protocol parameters are automatically calculated and will be displayed on the screen in a table. This table should be saved as source document and will be used to select the treadmill parameters for the constant work rate test (see below).

Should the subject reach or exceed 150 Watts (step 15), the incremental test will be repeated after at least 90 minutes later using 15 Watts/min (or 20 Watts/min for control subjects) slope. The repeat Incremental Exercise Test will recalculate the slope to 15 Watts/minute with a speed range of 0.6–3.0 mph and between 0 and 150 Watts. Similarly, a protocol with 20 Watt/min ramp slope will be generated for the control subjects.

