### *Phases of incremental test:*

**Start Time (TSTART):** Marks the beginning of the Incremental Exercise Test. TSTART begins after the 3 minute warm up, when the treadmill registers the speed and grade steps.

**Time to Maximal Effort (TMAX):** The subject will be encouraged to continue exercising for as long as possible and should be encouraged to complete the time point at which they begin to fatigue. Subjects should continue to exercise (i.e., to exhaustion or maximal exercise) until:

- Limited by symptoms (i.e., is unable to continue exercising because of the discomfort associated with the exercise) or desaturation (oxygen saturation  $\leq 85\%$  for at least 30 seconds)
- Unable to continue safely (in the opinion of the supervising physician).

The Incremental Exercise Time is the duration from TSTART until TMAX (maximal effort). This excludes the warm-up and recovery periods. (Incremental Exercise Time

(Duration)= $T_{MAX} - T_{START}$  (in minutes and seconds) that will be taken from the report. Subjects who are not able to walk more than 2 minutes due to severe dyspnea or leg pain are excluded from further study. If the subject is able to walk up to or exceed 15 minutes, the test will be repeated using a 15 or 20 Watt/min incremental protocol as described above.

**Recovery:** After the maximal effort is reached, the subject should continue to walk at the lowest speed (0.6 mph=1.0 km/h) and 0% grade for at least 3 minutes to prevent pooling the blood in the legs and to accelerate lactate removal. If the subject is unable to walk it is possible to offer sitting down on a chair put on the treadmill with feet put up horizontally.

**Determining the peak work rate:** The peak work rate is equivalent to the work rate of the step in which the subject requested to stop exercising as long as it was possible to complete that step for at least 30 seconds. Otherwise the peak work rate will be equivalent to the work rate of the last completed step.

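### Appendix 10.3's 25% grade limit cannot deliver 150 W at 2.2 mph to controls below about 64 kg, so a step-based peak can overstate some light controls' work rate

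*Protocol*

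**What the plan says.** Under Treadmill equipment, Appendix 10.3 states that "the slope range is from 0-25% grade". Under Incremental Exercise Challenge it sets the ramp at 10 W/min for COPD patients and "15 W/min for the age/ gender matched control subjects". It adds: "The target work rate (100 Watts in the COPD group and 150 Watts in the control group) is reached" at the tenth of 15 steps.

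One speed range is given and is not split by group: "The speed will be incremented linearly from 0.6 mph to 2.2 mph in the expected range", after which it "reaches a maximum of 4 mph in the extended range". Grade is then calculated from the speed and work-rate steps. The stated benefit is: "This design allows for each subject to perform the same work rate increment utilizing the same speed-range", whatever the subject weighs.

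The scoring rule is: "The peak work rate is equivalent to the work rate of the step in which the subject requested to stop exercising", provided that step was held for at least 30 seconds; otherwise the last completed step counts. The constant work rate is 80% of that peak, rounded to the nearest 5 W.

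The data-collection text says the exercise system also calculates TMWatt from the recorded treadmill settings and body weight. Section 2.4 lists "Maximum work rate during incremental exercise test" first among the COPD-versus-control endpoints.

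**The concern.** Once speed and work rate are fixed at each step, grade is the only quantity left to absorb differences in body weight, and a lighter subject needs a steeper belt. With a ceiling on grade, the ramp cannot be independent of weight: below some mass the treadmill cannot supply the step's wattage. The control ramp is half as steep again as the COPD ramp on the same stated speeds, so the ceiling falls almost entirely on controls.

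Peak is assigned from the step, not from delivered TMWatt. A light control can therefore be credited with more work than was done. That error runs one way: it raises control peaks and widens the apparent gap to COPD. The same inflated peak then sets the 80% constant load, so relative intensity may differ between the two populations.

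**Working it through.** **Inputs.** From Appendix 10.3: maximum grade 25%; 15 W/min (controls) and 10 W/min (COPD); 0.6 to 2.2 mph by step 10 and 4 mph in the extended range. From Section 3.3.1: BMI 18–35 kg/m² and no minimum weight. Assumed: work rate W = m × g × v × sin(arctan(grade)), with g = 9.81 m/s² and 1 mph = 0.44704 m/s; the stated speed range applies to controls; and the belt stays at 25% when more is called for.

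**The protocol's own figures.** 15 × 10 = 150 W and 10 × 10 = 100 W at step 10; 10 × 15 = 150 W at step 15 for COPD. All reproduce. Controls at step 15 would be at 15 × 15 = 225 W.

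**Minimum mass at step 10.** v = 2.2 × 0.44704 = 0.9835 m/s; sin(arctan 0.25) = 0.2425. Deliverable watts per kg = 9.81 × 0.9835 × 0.2425 = 2.340.
- Controls: 150 / 2.340 = 64.1 kg (62.2 kg if grade is taken as the sine).
- COPD: 100 / 2.340 = 42.7 kg.

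These weights are eligible: at 1.60 m, 64.1 kg is BMI 25.0 and 55 kg is BMI 21.5.

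**A control stopping at a nominal 150 W.** Delivered = 2.340 × mass; overstatement = 150 / delivered − 1.

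| Mass (kg) | Grade needed | Delivered (W) | Overstatement |
|---|---|---|---|
| 64 | 25.0% | 149.8 | 0.2% |
| 63 | 25.5% | 147.4 | 1.8% |
| 60 | 26.8% | 140.4 | 7% |
| 55 | 29.5% | 128.7 | 17% |
| 50 | 32.7% | 117.0 | 28% |

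**Other steps.** The limit depends on the step. The lower figure takes speed as rising 0.16 mph per step; the higher takes step 1 as 0.6 mph.

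| Step | Nominal W | Minimum mass (kg) |
|---|---|---|
| 5 | 75 | 50.4–53.8 |
| 7 | 105 | 57.4–59.2 |
| 8 | 120 | 60.0–61.2 |
| 9 | 135 | 62.2–62.8 |
| 10 | 150 | 64.1 |
| 11 | 165 | 60.6 |
| 15 | 225 | 52.9 |

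Steps 11 and 15 assume that speed rises linearly from 2.2 to 4 mph.

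**Constant load after a nominal 150 W peak.** 80% is 120 W, which is step 8.
- 62 kg: 120 W is delivered in full; true peak 145.1 W; 120 / 145.1 = 82.7%.
- 55 kg: 107.9–110.0 W is delivered; true peak 128.7 W; 84–86%. Against 0.8 × 128.7 = 103.0 W, the excess is about 5–7 W.

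**If reaching 150 W triggers a repeat test in controls.** Step 9 is then the last step that stands. Delivered = 135 × mass / minimum mass. At 55 kg this is 135 × 55 / 62.2 = 119.4 W, or 135 × 55 / 62.8 = 118.2 W, an overstatement of 13–14%. At 60 kg it is 129.0–130.2 W, or 4–5%.

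**The case against.** The strongest reply is that the reach is narrow and the premises are partly unseen.

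- **Premises.** No work-rate formula is printed. The step tables are generated per subject in the RDC system, and further detail sits in a Manual of Procedures that is not shown. The one other 15 W/min ramp to 150 W, the COPD repeat test, uses 0.6–3.0 mph, where the minimum mass is only 47.0 kg. If controls used that range, little would remain. This stands as a condition on the finding. The text as written nevertheless states a single range and promises weight independence, with no rule for a required grade above 25%.
- **Reach.** A reader might infer that every control under 64 kg has an inflated peak. That does not follow. The 64 kg figure belongs to step 10. A 62 kg control who stops at step 8 or earlier, or at step 11 or later, is scored correctly. The share of controls below 64 kg would be at most a ceiling on those affected, and the protocol gives neither a weight distribution nor a distribution of attained peaks.
- **Constant load.** A reader might also infer that the 80% load is undeliverable below 64 kg. It is fully deliverable down to about 60–61 kg. The load is also only a starting value: Section 5.1.1 checks exercise duration at Visits 2 and 3 for all participants and adjusts the load if needed. That stands, but it does nothing for the recorded peak.
- **Repeat rule.** Section 5.1.1 repeats the incremental test at 150 W or more, so step 10 may not be a control's final result. Appendix 10.3 ties the same trigger to step 15 and to 15 minutes, which matches 150 W only on the COPD ramp. Under the literal reading the error still arises at step 9 and below. If the 20 W/min repeat ran at 0.6–3.0 mph to 200 W (neither is stated), it would need 62.7 kg.

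**Conclusion.** The grade limit, the stated speed range and the claim of weight independence cannot all hold for controls below about 64 kg (62 kg if grade is read as the sine). This rests on the vertical-work formula and on the 0.6–2.2 mph range applying to controls. Where a control's test ends on a step at which the limit binds, the step-based peak overstates delivered work. At 63–64 kg this is negligible; it becomes material from about 60 kg downwards. The 28% at 50 kg is a corner case, needing a very light control who stops at exactly a nominal 150 W. The starting constant load can be about 83–86% of true peak.

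The documents do not support any claim about how many controls are affected, nor any threat to the treatment comparison. Section 7.3.2 summarises the COPD-versus-control endpoints descriptively, controls are never randomised, and the COPD ramp reaches 100 W down to about 43 kg. Characterising exercise limitation against controls is still a stated objective, and this error has a direction, so it is worth correcting.

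**What to change.** In Appendix 10.3, define peak work rate in both groups as delivered TMWatt over the final step if it was held for at least 30 seconds, otherwise over the last completed step. Derive the 80% load from that figure.

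Then reconcile the 25% limit, the control speed range and the weight-independence sentence. State what happens when a subject's table calls for more than 25%, and whether the 150 W repeat trigger applies to controls at step 10. Redefining peak does not settle this alone. At 55 kg, 80% of 128.7 W rounds to 105 W, which is step 7 and needs 57.4–59.2 kg at that step's speed.

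A faster speed range for light subjects only would cure the shortfall but make walking speed depend on weight, which the design sets out to avoid, so it is not recommended.

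The cost is a small change to the RDC calculation and a few sentences of text; TMWatt is already calculated.

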### ***ECG and Safety monitoring***

- ECG recordings will be monitored during all exercise challenges.
- Blood pressure will be determined before exercise, at the peak of exercise and five minutes after termination of exercise and when, for clinical reasons, it is required. At the same time points heart rate will be determined from ECG.

### ***Personnel qualifications***

- Exercise challenges should be conducted by adequately trained personnel with a basic knowledge of exercise physiology.
- Technicians familiar with normal and abnormal responses during exercise and trained in CPR should be present throughout the test.
- Technicians must be certified by Boehringer-Ingelheim staff (or their designee) to perform exercise testing for this clinical trial. A copy of each site staff's certification must be filed in the ISF.
- The supervising physician must be readily available to respond as needed. The degree of subject supervision should be increased if warranted by the clinical status of the subject.

### ***Safety issues***

**Subjects will not be allowed to perform an exercise challenge if they are known to have or are suspected of having one of the following contra-indications:**

- Recent myocardial infarction (i.e., within one year or less)
- Unstable angina
- Unstable, life-threatening or uncontrolled cardiac arrhythmias causing symptoms, haemodynamic compromise, requiring intervention or change in drug therapy during the last year
- Active endocarditis
- Acute myocarditis or pericarditis
- Symptomatic severe aortic stenosis
- Uncontrolled heart failure
- Acute non-cardiac disorder that may affect exercise performance or be aggravated by exercise (i.e., infection, renal failure, thyrotoxicosis)
- History of thrombosis and / or pulmonary embolism
- Left main coronary stenosis or its equivalent
- Moderate stenotic valvular heart disease
- Electrolyte abnormalities
- Severe untreated arterial hypertension (>160 mmHg systolic, >100 mmHg diastolic)
- Significant pulmonary hypertension
- Tachyarrhythmias or bradyarrhythmias
- Hypertrophic cardiomyopathy
- Mental impairment leading to inability to cooperate
- High-degree atrioventricular block
- Cardiac (bradyarrhythmias, ventricular tachycardia, myocardial infarction, heart failure, hypotension, and shock) and non-cardiac (musculoskeletal trauma, severe fatigue,

dizziness, fainting, body aches) complications of exercise challenges have been reported. Consequently during the test, study personnel should be alert to any abnormal event.

- Indications to stop the test must be clearly established and known by the personnel involved in testing:

Symptoms such as:

- acute chest pain,
- sudden pallor,
- loss of co-ordination,
- mental confusion,
- extreme dyspnea.

Signs such as:

- clinically significant abnormalities in ECG recordings during exercise. This includes horizontal depression of ST segment  $> 0.2$  mV, T-wave inversion, sustained ventricular tachycardia, polymorphic and / or frequent premature ventricular beats, couplets or triplets particularly of multifocal origin.
  - progressive fall in systolic pressure of 20 mmHg or more less than the previous measurement or below the resting value during exercise.
  - Exercise induced hypertension  $>250$  mmHg systolic and/or  $>115$  mm Hg diastolic.
- If the exercise test has been stopped for one of these reasons, the subject should be monitored in the laboratory until signs/symptoms/ECG abnormalities have completely cleared. Full CPR equipment should be available in the laboratory. In case the exercise test was stopped because of any of the above detailed medical reasons **the subject will be withdrawn from the study.**

